## Abstract

**Background:**

Traditional one-session exposure therapy (OST) in which a patient is gradually exposed to feared stimuli for up to 3 h in a one-session format has been found effective for the treatment of specific phobias. However, many individuals with specific phobia are reluctant to seek help, and access to care is lacking due to logistic challenges of accessing, collecting, storing, and/or maintaining stimuli. Virtual reality (VR) exposure therapy may improve upon existing techniques by facilitating access, decreasing cost, and increasing acceptability and effectiveness. The aim of this study is to compare traditional OST with in vivo spiders and a human therapist with a newly developed single-session gamified VR exposure therapy application with modern VR hardware, virtual spiders, and a virtual therapist.

**Methods/design:**

Participants with specific phobia to spiders (*N* = 100) will be recruited from the general public, screened, and randomized to either VR exposure therapy (*n* = 50) or traditional OST (*n* = 50). A behavioral approach test using in vivo spiders will serve as the primary outcome measure. Secondary outcome measures will include spider phobia questionnaires and self-reported anxiety, depression, and quality of life. Outcomes will be assessed using a non-inferiority design at baseline and at 1, 12, and 52 weeks after treatment.

**Discussion:**

VR exposure therapy has previously been evaluated as a treatment for specific phobias, but there has been a lack of high-quality randomized controlled trials. A new generation of modern, consumer-ready VR devices is being released that are advancing existing technology and have the potential to improve clinical availability and treatment effectiveness. The VR medium is also particularly suitable for taking advantage of recent phobia treatment research emphasizing engagement and new learning, as opposed to physiological habituation. This study compares a market-ready, gamified VR spider phobia exposure application, delivered using consumer VR hardware, with the current gold standard treatment. Implications are discussed.

**Trial registration:**

ClinicalTrials.gov identifier NCT02533310. Registered on 25 August 2015.

## Background

Specific phobias are second only to major depression for lifetime prevalence of mental health disorders in the United States (16.6 % vs 15.6 %) [1]. The prevalence is somewhat reduced in older individuals (8.7 %) [2]. Estimates suggest 60–80 % of those with specific phobia are hesitant to seek help [3]. Some phobias are far more common than others [4], with half of reported phobias being fear of either heights or animals [5]. Spider phobia is among the most prevalent of animal phobias and is the most studied. The consequences of anxiety, worry, and avoidance behavior can have a large impact on quality of life, work, and leisure activities [6].

Exposure-based therapies in which an individual is systematically and repeatedly presented with a feared or avoided internal or external cue is highly effective in reducing anxiety disorders [7, 8]. Compared with imaginal exposure, evidence indicates that an in vivo (naturalistic setting) stimulus is the preferable exposure treatment method for specific phobia [6]. One-session therapy (OST) is considered the intervention of choice for in vivo specific phobia treatment in adults and children [9, 10]. OST sessions typically last up to 3 h and consist of graduated exposure to phobic stimuli, positive reinforcement, therapist modeling of non-phobic behavior, and cognitive restructuring of catastrophic beliefs [11].

The benefits of exposure therapy are limited by issues pertaining to both therapist and patient. Access to evidence-based treatments has been lacking [12], likely commensurate with the challenges of therapists locating appropriate material and/or stimuli, difficulties with conducting exposure work outside the clinic, and maintaining stimuli such as animals and insects. Even when these resources are available, participants may refuse to engage in therapy. Once explained, exposure therapy is turned down by 30 % of subjects [13], and this percentage is estimated to be significantly higher for OST if the endpoint is discussed beforehand [12]. Return of fear of the feared stimuli following treatment can also occur at a later date [14].

Virtual reality (VR) technology involving head-mounted, motion-tracked displays, accompanied by realistically rendered 3D computer-animated environments [15], offers researchers the opportunity to recreate phobic stimuli, manipulate and tailor key variables associated with stimulus presentation (color, size, and movement), context, scheduling, and intensity of exposure according to the patient’s needs, as well as to extract unprecedented amounts of data, such as gaze focus [16]. Previous generations of VR have already been used successfully in mental health treatments [17] for fear of flying, heights, public speaking, and spider phobia, among others [18]. VR thus has the potential to greatly increase accessibility and effectiveness of exposure treatments. In a survey of 777 undergraduate students who scored high in fear of spiders, more than 80 % expressed a preference for VR exposure treatment over in vivo treatment [19]. In recent studies, researchers have evaluated the unique opportunity of VR to inexpensively and relatively easily alter the context of exposure, an important moderator of treatment resurgence [20]. Participants treated using VR in multiple environments [21], and participants treated by exposure to spiders using video recordings of multiple areas of a house rather than a single area [22], were less likely to have return of fear following an aversive event.

Serious games designed for purposes other than entertainment and allowing users to experience situations impossible or dangerous in real life [23], with gamified elements such as points and goals to increase engagement [24], may provide a particularly promising advancement in exposure therapy. As reviewed by Botella et al. [25], game elements may reduce distress as compared with traditional exposure therapy [26]. Recommendations that patients continue to confront phobic stimuli posttreatment [12] may be facilitated by gamified VR content that can be played again and again [25].

The potential of VR notwithstanding, the quality of past VR exposure therapy research has historically been poor [27]. Well-designed randomized controlled trials are required before implementation in clinical practice can be recommended. Further, recent advances in VR technology have enabled unprecedented realistic stimuli to be rendered with less intrusive equipment, minimizing the risk of nausea and allowing longer sessions, though careful application design is still required [28]. A new generation of VR systems produced by some of the world’s largest technology companies, such as Sony (Project Morpheus), Microsoft (Hololens), HTC (Vive), and Facebook (Oculus Rift), promises to change VR from a professional niche product costing as much as $35,000 to a consumer product priced around $599 plus the cost of a competent computer [29]. Other developments in VR include the use of smartphone-based systems such as the Samsung Gear VR, used in the present study, the cost of which is negligible ($99 USD) if paired with a user’s preexisting smartphone [30]. From a research perspective, using VR can also reduce some of the complexity of carrying out exposure treatments, improve standardization of protocols and cost-effectiveness, and enable at-home self-care [31].

The parallel-group randomized controlled trial described in this protocol is designed to investigate non-inferiority of a novel, gamified VR OST program for spider phobia by comparison with traditional OST.

## Methods/design

This randomized controlled trial is registered in the ClinicalTrials.gov database (NCT02533310) and has received ethical approval from the Stockholm Regional Ethical Review Board (Dnr 472-31). Written informed consent will be obtained from all participants at the premeasurement occasion.

### Procedure

To recruit a diverse sample, multiple recruitment methods will be used, primarily postings in online forums and through coverage in national television, newspapers, and magazines [32]. Potential participants will be directed to the study website (www.vimse.se), where they will find more information about the study and can complete the online screening battery. Participants meeting inclusion criteria will travel to Stockholm University to complete the premeasurement, including self-rating scales, a diagnostic interview, and a Behavioral Approach Test (BAT). If suitable for inclusion, participants will be randomized and, approximately 1 week after the premeasurement occasion, will complete the allocated treatment session. Posttreatment measurements will take place approximately 1 week after the treatment session. Additional follow-up measurements are planned after 12 and 52 weeks. See Fig. 1 for the study flowchart.

**Fig. 1 Fig1:**
[figure not shown]
Study flowchart. *BAT* Behavioral Approach Test

Subjects will be randomized to treatment arms (using a true random number generator: www.random.org) after completing the premeasurement in preset blocks of 4, 6, 8, or 10 (randomly sized) with even group allocation in each block. Randomization will be performed by a research assistant not otherwise involved in the study, and allocation will be blinded to all but the treatment coordinator and the assigned therapist. As in most psychological research, blinding participants to treatment allocation is not feasible. For ethical reasons, subjects are informed at premeasurement of the two possible treatment allocations, and their preference (and strength thereof) is noted to enable investigation of mediating effects of treatment preference. The therapist administering the posttreatment assessment will be blinded to treatment allocation until all outcome measures have been completed.

All data gathered during the study will be stored anonymously. No contractual agreements limit access by other investigators to this data or to final datasets, and upon completion the dataset generated in this trial will be published in a data repository (e.g., Dryad or figshare), accompanied by the script files to reproduce the statistical analyses.

### Sample

The sample will consist of 100 adults (age ≥18 years). To be included, participants need to reside in Sweden, be fluent in Swedish, and have the ability to travel to the study location on five separate occasions (pretest, treatment, posttest, and two follow-up occasions). Exclusion criteria include ongoing psychotherapy or psychotropic medication (unless on stable dosage for the previous 3 months and no changes planned during the study period), indications of suicidal ideation or other serious mental disorder (e.g., substance misuse, bipolar disorder, psychosis), and lack of stereoscopic vision or balance problems that would hinder experiencing the VR environment. To meet inclusion criteria, participants must score 9 or less on the BAT (see below) and meet the criteria set forth in the *Diagnostic and Statistical Manual of Mental Disorders, Fifth Edition* (DSM-5), for specific phobia, assessed using the Structured Clinical Interview for DSM Disorders [33] adapted for DSM-5 criteria [34].

### Measures

#### Primary outcome measure

Change from baseline on the BAT will serve as the primary outcome measure. To study the real-world effects of VR therapy, all participants will complete the same BAT featuring a real spider. The BAT [35] will feature 13 steps (scored 0–12) corresponding to sequentially closer contact with the spider. See Table 1 for sequence details. The BAT will begin with participants standing outside a room (approximately 3 × 5 m large) where there will be a table placed farthest away from the door, on which a transparent container (about 40 × 30 × 19 cm large) will house the spider (medium-sized; see below). The participants will be informed that the objective of the exercise is to pick up and hold the spider in their hands for 20 seconds. They will be encouraged to do their best but will be told that they can abort the exercise at any time. A pretreatment score of 9 or less [36] will be required for study inclusion.

**Table 1 Tab1:** Behavioral Approach Test step specifications

Score	Details
0	Refusal to enter room
1	Enters room but stops before covering one-fifth of the distance to the container
2	Stops before covering two-fifths of the distance to the container
3	Stops before covering three-fifths of the distance to the container
4	Stops before covering four-fifths of the distance to the container
5	Stops before covering all of the distance to the container
6	Reaches the table with the container
7	Touches the container
8	Removes the lid of the container
9	Puts a hand inside the container
10	Touches the spider with at least one finger
11	Holds spider in hands for less than 20 seconds
12	Holds spider in hands for 20 seconds or more

#### Secondary outcome measures

In addition to the BAT, subjects will complete two self-report measures of fear toward spiders: the Spider Phobia Questionnaire (SPQ) [37] and the Fear of Spiders Questionnaire (FSQ) [38]. The Generalized Anxiety Disorder 7-item scale (GAD-7) [39] will be used to measure generic anxiety symptoms, and the Patient Health Questionnaire-9 (PHQ-9) [40] will be used to evaluate depression symptoms. Subjective quality of life will be measured with the Brunnsviken Brief Quality of life scale (BBQ) [41]. Meeting diagnostic criteria for specific phobia in the 12- and 52-week follow-up measurements will also serve as a secondary outcome measure. Swedish translations of all the self-rating scales will be used.

#### Other measures

At premeasurement, all participants complete the treatment Credibility/Expectancy Questionnaire (CEQ) [42] for both the traditional OST and VR treatments (in quasi-randomized order). Participants also complete the CEQ at postmeasurement with re-phrased items that ask respondents to evaluate their completed treatment. A number of additional surveys will be used to determine the influence of moderating factors on VR treatment outcome. Immediately following treatment, VR-treated participants will answer the Simulator Sickness Questionnaire (SSQ) [43], a measure of participant discomfort during treatment. At postmeasurement, VR-treated participants will further complete the iGroup Presence Questionnaire (IPQ) [44], a measure of the sense of actually being in the virtual environment, and the System Usability Scale (SUS) [45], which assesses product complexity and ease of use. At postmeasurement, all participants will complete the Adverse Effects Questionnaire, a novel measurement tool used to assess side effects of psychological treatments, as proposed by Rozenthal et al. [46]. Finally, at 12-week and 52-week follow-up, patients will answer questions regarding frequency and type of interactions with spiders since their last visit, as well as other forms of treatment received.

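### The only side-effect questionnaire given to both arms is scheduled once, about 1 week after treatment, while outcomes are followed to 52 weeks

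*Protocol article*

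**What the plan says.** The Other measures section of the protocol article gives each additional instrument its own time point. For side effects it says: "At postmeasurement, all participants will complete the Adverse Effects Questionnaire, a novel measurement tool used to assess side effects of psychological treatments". The Procedure section dates that occasion and the later ones: "Posttreatment measurements will take place approximately 1 week after the treatment session. Additional follow-up measurements are planned after 12 and 52 weeks".

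The same part of Other measures states what is added at the late visits: "at 12-week and 52-week follow-up, patients will answer questions regarding frequency and type of interactions with spiders since their last visit". Participants are also asked there about any other treatment they have had. Adverse effects are not on that list.

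Efficacy is followed for longer. The Abstract says: "Outcomes will be assessed using a non-inferiority design at baseline and at 1, 12, and 52 weeks after treatment". The Background acknowledges that relapse may come late: "Return of fear of the feared stimuli following treatment can also occur at a later date".

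One discomfort measure is taken on the day of treatment, the Simulator Sickness Questionnaire (SSQ). Other measures assigns it to VR-treated participants only.

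**The concern.** The trial will compare benefit between VR and traditional OST out to 52 weeks, but its structured, participant-reported comparison of side effects stops at about week 1. Anything the questionnaire would have picked up after that has a stated route into the data only if it also moves an outcome scale.

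On the treatment day itself, a questionnaire on discomfort is stated for one arm and not for the other, so the arms cannot be compared at that time.

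The application is presented as close to market, and the Background sees possible gains in acceptability. A conclusion that VR is no worse than OST to one year would then stand beside a side-effect comparison covering a much shorter period. Reports that are not collected at the visits cannot be recovered by analysis afterwards.

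**Working it through.** The plan gives no figure on this point to reproduce. The check is a comparison of the stated schedule, instrument by instrument.

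**Post-treatment occasions** (Procedure; Abstract): about week 1, week 12 and week 52, which makes 3 visits.

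| What is recorded | Arms | Treatment day | Week 1 | Week 12 | Week 52 | Section |
|---|---|---|---|---|---|---|
| Adverse Effects Questionnaire | both | not stated | yes | not stated | not stated | Other measures |
| SSQ | VR only | yes | – | – | – | Other measures |
| BAT | both | – | yes | yes | yes | Abstract; Primary outcome measure |
| SPQ, FSQ, GAD-7, PHQ-9, BBQ | both | – | yes | yes | yes | Abstract; Secondary outcome measures |
| Specific phobia diagnosis as an outcome | both | – | – | yes | yes | Secondary outcome measures |
| Spider encounters, other treatment | both | – | – | yes | yes | Other measures |

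**Step 1: coverage of the side-effect instrument.** It is given at 1 of 3 post-treatment visits. The intervals without it run from week 1 to week 12 (12 − 1 = 11 weeks) and from week 12 to week 52 (52 − 12 = 40 weeks). These are lengths of follow-up. They say nothing about the share of side effects that fall in them, and effects of a single session may well cluster early.

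**Step 2: what the late outcome measures already catch.**
- Return of fear is caught by the BAT, SPQ, FSQ and diagnosis.
- General worsening is caught by GAD-7 (anxiety), PHQ-9 (depression) and BBQ (quality of life).
- All of these are scored for each participant. All but diagnosis are also compared with a baseline score, so deterioration can be counted per person and per arm.

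**Step 3: what is left.**
- Side effects outside those domains that arise after week 1 have no stated instrument.
- An effect that starts and settles between two visits may leave no trace in a score taken at the visit. The late-visit questions on spider encounters do look back over the interval, so the possible trigger is asked about but any unwanted effect is not.
- None of the outcome scales is described as asking whether the participant links a change to the treatment.
- Diagnosis cannot separate harm from non-response. The Sample section requires every participant to meet the criteria at entry, so still meeting them later may mean only that treatment did not work.

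**Step 4: treatment day.** The SSQ gives a same-day questionnaire in VR and nothing equivalent is stated for OST. Subjective distress ratings are taken during the session in both arms, but in OST they are described as steering progress through the exposure steps, and neither arm's ratings are described as a report of side effects. The week-1 questionnaire can pick up session effects by recall in both arms, but only from those who attend.

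**The case against.** The strongest reply is that the article has little left to miss. Return of fear, the late risk it names, is measured at 12 and 52 weeks by a live-spider test, two fear scales and a diagnostic assessment. Three general scales cover wider worsening. A psychologist or therapist is present one-to-one in both arms, and treatment is a single session of at most 3 h. A condensed article may also leave spontaneous adverse-event reporting to the full protocol.

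Much of this stands, and it rules out several stronger readings that a reader might infer:

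- That late harms in general, or the named late risk, are missed. They are not; the repeated outcomes capture return of fear and general worsening participant by participant.
- That someone who becomes more fearful after a spider encounter during follow-up is never asked. That person reports the encounter and completes the fear and distress measures at the next visit. What is absent is a question about side effects and their link to treatment.
- That treatment-day discomfort goes unrecorded in both arms. The VR arm has the SSQ.
- That participants who skip the week-1 visit are lost to harms reporting. How non-attenders and interrupted sessions are followed up is a detail that an article commonly leaves to the full protocol, so its absence here shows nothing.

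The reply does not remove the narrower point. The timing of the Adverse Effects Questionnaire is stated, as are the items added at the late visits, so this is a schedule the article fixes and not something it leaves open. Spontaneous reporting, if it exists, would not replace a structured question put to every participant in both arms. The choice of a separate side-effect instrument also suggests that the outcome scales alone were not thought sufficient.

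**Conclusion.** The point holds in a limited form. The one participant-reported side-effect instrument common to both arms is scheduled at 1 of 3 post-treatment visits. Side effects outside fear, anxiety, depression, quality of life and diagnosis that arise after week 1, or that come and go between visits, have no stated systematic capture. Same-day discomfort is asked by questionnaire in one arm only.

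No number of missed effects can be given, because the article states neither an expected side-effect rate nor a dropout rate. The conclusion rests on reading the visit assignments in Other measures as complete for the instruments they list. It is an improvement worth making to the harms comparison. It does not touch the primary non-inferiority analysis.

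**What to change.** In Other measures, schedule the Adverse Effects Questionnaire for both arms at two further points:

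1. At the existing 12- and 52-week visits, with items covering the time since the previous visit.
2. At the end of the treatment session in both arms, so that OST has a same-day record as well as VR.

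Report counts per arm and per window (session, to week 1, weeks 1 to 12, weeks 12 to 52), each with the number treated and the number responding.

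The cost is a few more minutes per participant on occasions that already take place, and a minor amendment. The Trial status section says that recruitment was ongoing at submission in August 2015, so anyone already treated by then cannot give the same-day questionnaire. The numbers responding in that window should show this.

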### Interventions

#### Traditional OST

Traditional OST treatment sessions will be held with participants on a one-to-one basis with clinical psychologists or clinical psychologists in their final year of training, all with past clinical cognitive behavioral therapy experience. All OST therapists will receive regular supervision from an experienced clinical psychologist and psychotherapist.

Traditional OST for spider phobia consists of a combination of gradated exposures to increasingly large, naturally occurring in vivo spiders and model learning of healthy, non-phobic behavior as demonstrated by the therapist [12]. Spiders used in traditional OST (and the BAT) will be harmless common varieties indigenous to the region, primarily of the genus *Tegenaria* (*T. domestica* and *T. atrica*). Spiders will be classified according to size: small (5–15 mm), medium (15–25 mm), or large (>25 mm).

The goal of OST is to bring patients a greater sense of control and a recognition that their feared catastrophic outcome will not occur (e.g., they will not have a heart attack). OST is performed for a maximum 3-h duration during a morning or afternoon. The patient is first explained the rationale and content of the treatment, then their catastrophic beliefs and safety behaviors are explored and avoidance activities are normalized. Participant modeling encourages careful observation by patients and that they not close their eyes or look away. Subjective units of distress (SUD) ratings are used to determine when to move on to a more challenging stage of treatment (100 % denotes the most anxiety-provoking situation experienced in relation to the phobia). Humor can be used to put the patient’s reactions into perspective and reduce the patient’s anxiety [47].

The initial graduated exposure step (featuring a small spider) teaches the patient to capture a spider with a glass with the intention of removing it from the building. The next exposure step has the patient touch various parts of the spider. Interactions with the spider are best organized as behavioral experiments in which the patient’s beliefs about what may occur are tested against reality. The exposure steps that follow have the spider crawl first on the patient’s hand then up to the elbow, and finally the spider is allowed to crawl on the patient’s body, from the knee to the waist and from the shirt up to the neck. These steps are then repeated using first a medium spider and then a large spider. The final stage has the patient handle two spiders, one in each hand, and an overlearning step can be added in which the spider crawls on the patient’s hair and cheek. The patient should have no or low anxiety in the last exposure stages and should no longer believe their catastrophic cognitions.

